## Abstract

**Background:**

Mobility impairment and participation restrictions are commonly experienced by individuals with autosomal recessive spastic ataxia of Charlevoix-Saguenay (ARSACS) and myotonic dystrophy type 1 (MD1), 2 disorders that are highly prevalent in the province of Quebec, Canada. People with ARSACS and MD1 experience a progressive decline in mobility, which commonly results in the provision of manual or power wheelchairs. While wheelchairs can facilitate mobility and social participation, their provision alone does not guarantee safe and effective use. Wheelchair skills training has been shown to be effective for improving manual skills and confidence among adult users with various diagnoses, which may enhance self-directed mobility and participation and reduce the risk of chronic and acute injuries. However, manual wheelchair skills training for people with ARSACS and MD1 remains understudied.

**Objective:**

The primary aim of this study is to evaluate the efficacy of manual wheelchair skills training for safely improving wheelchair performance in people with ARSACS and MD1. The secondary outcomes include exploring the influence of manual wheelchair skills training on skill capacity, use self-efficacy, mobility, and the retention of outcomes 3 months later. We will also qualitatively explore the manual wheelchair training experiences of people with ARSACS and MD1.

**Methods:**

This study will use a sequential multimethods design, combining a waitlist randomized controlled trial and qualitative interviews. The participants will include adults who have a diagnosis of ARSACS or MD1 who use a manual wheelchair for mobility. Participants will be randomly assigned to the intervention or control group using a 1:1 allocation ratio. The intervention group will receive 5 manual wheelchair skills training sessions (1-2 sessions/week), while the control group will receive no training. Data will be collected at baseline (T1), after the 4-week intervention (or waiting period for the control group; T2), and 3 months after T2 to assess retention (T3). The primary outcome will be manual wheelchair skills performance. Secondary outcomes will include manual wheelchair skills capacity, self-efficacy, and mobility. Semistructured individual interviews will be conducted to explore participants’ expectations regarding manual wheelchair use, past manual wheelchair experiences, and perceptions of manual wheelchair skills training. Quantitative data will be analyzed using analysis of covariance (ANCOVA), controlling for baseline scores, and qualitative data will be analyzed using reflexive thematic analysis.

**Results:**

This study received ethical approval (2025-3100) in July 2024. Recruitment started in January 2025. A graduate student, a research assistant, and a research coordinator have been recruited and trained.

**Conclusions:**

The results of this randomized waitlist-controlled trial will confirm whether manual wheelchair skills training can improve self-directed mobility and related outcomes for people with ARSACS and MD1. The findings may help guide clinical practice toward manual wheelchair skills training for understanding potential influences on manual wheelchair mobility in people living with neuromuscular disorders.

**Trial Registration:**

ClinicalTrials.gov NCT06596850; https://clinicaltrials.gov/study/NCT06596850

**International Registered Report Identifier (IRRID):**

PRR1-10.2196/66974

## Introduction

Mobility impairment and participation restrictions are commonly experienced by people with neuromuscular and hereditary degenerative disorders [1]. Two highly prevalent disorders in the province of Quebec include autosomal recessive spastic ataxia of Charlevoix-Saguenay (ARSACS) [2,3] and myotonic dystrophy type 1 (MD1) [4,5]. Declining mobility is a hallmark among people with ARSACS and MD1 that can negatively influence physical and psychosocial health outcomes. Approximately 74% of individuals with MD1 have mobility impairments that restrict participation in activities of daily living, leisure activities, and vocation [6-8].

Wheelchairs (manual or power) are prescribed to facilitate mobility for people with ARSACS and MD1 when walking becomes difficult. In the reported literature, approximately 45% of individuals with ARSACS use wheelchairs [9-11], with the average age of wheelchair provision at 38.9 years [10]. Given the varying rate of progression of ARSACS, wheelchairs may be suggested during adolescence or older age (eg, 17 to 59 years of age) [12], but most people (if not all) will eventually need one for mobility. A patient registry of MD1 in the United Kingdom reported that 56% of patients used a wheelchair, with the average age at which wheelchair use began being 34.6 years, ranging from infancy to old age (1 to 72.4 years). Among the wheelchair users in this registry, 22.8% started using it before the age of 10 years and 56.6% began between 30 and 59 years of age [13].

Regardless of diagnosis or type of wheelchair (ie, manual or power), wheelchair provision alone does not guarantee safe and effective use. If not used adequately, wheelchairs could be associated with mobility dependence, restricted participation, reduced social connectedness [14], and reduced quality of life [15]. Moreover, unsafe wheelchair use could lead to accidents that vary in severity from cuts and bruises to life-threatening head injuries [16]. Furthermore, injuries due to wheelchair accidents may increase caregiver burden and strain on the health care system [17].

Learning how to use the wheelchair and developing appropriate wheelchair skills are critical to independent mobility and participation [18]. However, wheelchair mobility for people with ARSACS and MD1 remains understudied. Our team recently demonstrated that adults with ARSACS had lower manual and power wheelchair skills but fewer training goals than adults with other diagnoses (eg, spinal cord injury) [19]. This disparity may be attributed to limited training opportunities and low expectations of wheelchair use for individuals with ARSACS [19]. It may be that the progressive nature of ARSACS and MD1 (and other neuromuscular disorders) and the clinical focus on maintaining functional walking have historically taken clinical precedence over wheelchair mobility outcomes.

The World Health Organization suggests training in wheelchair use and follow-up as important steps in wheelchair service provision [20]. Four meta-analyses demonstrate the effectiveness of wheelchair skills training for improving wheelchair skills, use confidence, and participation [20-23]. However, a survey of 68 Canadian rehabilitation centers demonstrated that >50% of therapists spent 2 hours or less on wheelchair skills training and 18% provided no training at all [24]. Moreover, individuals with ARSACS and MD1 do not typically spend periods of time in rehabilitation centers where most wheelchair skills training occurs. The inherited and progressive nature of ARSACS and MD1 means that people receive wheelchairs when they can no longer walk but do not commonly receive additional assessments, training, or follow-ups related to wheelchair use. Given the evidence on the effect of manual (manual wheelchair) skills training in other progressive conditions (eg, multiple sclerosis, Parkinsonism) [22,23], the association between manual wheelchair mobility and the preservation of upper limb function and strength in ARSACS [19], it is likely that evidence-based training could improve manual wheelchair skills, confidence, and social participation for people with ARSACS, MD1, and other neuromuscular disorders. In a pilot study, 3 individuals with ARSACS improved their manual wheelchair skills (between 18% and 30%) and confidence (between 5% and 15%) after 3 hours or less of manual wheelchair skills training [25].

The overall aim of this study is to evaluate the efficacy of an evidence-based manual wheelchair skills training program for improving safe manual wheelchair mobility in people with ARSACS and MD1. The primary objective is to test the hypothesis that participants who receive manual wheelchair skills training will improve their manual wheelchair performance by at least 20% compared to those in a control group who receive no training. The secondary objectives are to explore the influence of manual wheelchair skills training on wheelchair skills capacity, use self-efficacy, and mobility. Finally, the participants’ expectations regarding manual wheelchair use and the experiences and perceived impact of manual wheelchair skills training on mobility and quality of life will be explored using a qualitative inquiry.

## Methods

### Study Design

A sequential multimethods randomized controlled trial (RCT) and qualitative interviews will be used, with the RCT reported according to the CONSORT (Consolidated Standards of Reporting Trials) guidelines [26]. Participants will be randomly assigned to the intervention or control group using a 1:1 allocation ratio. A randomization process with undisclosed block size will be created by a statistician who is not otherwise involved in the project. Given the potential benefits of the intervention already reported in our previous studies [22,23], control group participants will also receive wheelchair skills training following a 4-week control period and postintervention data collection (ie, they will be on a “waitlist” for the wheelchair skills training program and receive no intervention during the study period).

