### Ethical Considerations

The protocol for this study was approved by the Research Ethics Boards in rehabilitation and social integration of the Centre Intégré Universitaire de Santé et de Services Sociaux de la Capitale-Nationale (CIUSSS-CN; 2025-3100). The study protocol was registered on ClinicalTrials.gov (NCT06596850). Informed consent will be obtained from all participants by a research coordinator (RC). Participants will be made aware that they can withdraw from the study at any moment without facing any consequences. All collected information will remain strictly confidential within the limits established by law. To protect privacy and confidentiality, participants will be identified by a unique code, and their data will be anonymized and securely stored on a password-protected server. Participants will receive financial compensation for data collection activities to acknowledge their time and reduce attrition (CAD $50, equivalent to US $36, after each assessment session).

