### Study Procedures

Following enrollment, participants will complete baseline measures (T1) and then be assigned to either the experimental or the control group. An RC will then contact the statistician via telephone or email to obtain the group assignment within 48 hours. The participant will be informed of the group assignments, and the trainer will be given the participants’ contact information to schedule the training sessions and assign the control group. The training will be scheduled after completing the blinded postintervention data collection (T2). In an effort to minimize bias, a research assistant (RA) will be blinded to group allocation and participants will be instructed not to discuss their program with the RA. The RC will also arrange for the blinded follow-up (retention) data collection for all participants 3 months after postintervention data collection (T3). Qualitative interviews will be conducted by the RC by phone or videoconferencing within 7 days of completing the intervention. Given the self-report nature of the primary outcome, the interdisciplinary experience of 3 study investigators with RCTs who are not located at the data collection site, and the involvement of a citizen partner and Muscular Dystrophy Canada in data collection, analysis, and interpretation, a data monitoring committee was not established. Participants in the intervention and control groups will continue to receive usual care (if any) during the study. The trial design describing coordination, testing, and experimental procedures is depicted in Figure 1.

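### The research coordinator who consents every participant also receives every assignment, so the next arm can be guessed better than chance before each new consent

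*Protocol article*

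**What the plan says.** On the sequence, Study Design states "Participants will be randomly assigned to the intervention or control group using a 1:1 allocation ratio" and "A randomization process with undisclosed block size will be created by a statistician who is not otherwise involved in the project". It does not say whether the block size is fixed or varies.

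On consent, Ethical Considerations states "Informed consent will be obtained from all participants by a research coordinator (RC").

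On timing and release, Study Procedures states "Following enrollment, participants will complete baseline measures (T1) and then be assigned to either the experimental or the control group", followed by "An RC will then contact the statistician via telephone or email to obtain the group assignment within 48 hours". The participant is then told the group, without saying by whom, and the trainer is given contact details to schedule sessions.

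On staffing, the Results paragraph of the abstract reports "A graduate student, a research assistant, and a research coordinator have been recruited and trained", that is, one RC.

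On blinding, Study Procedures says only that "a research assistant (RA) will be blinded to group allocation". The same section acknowledges the nature of the endpoint: "Given the self-report nature of the primary outcome".

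**The concern.** Concealing the current assignment is one protection; keeping the next one unpredictable is another. The first is in place: an outside statistician holds the list, and nothing is released until consent and T1 are complete. The second is weakened by the RC's two tasks. Before approaching the next candidate, the RC has already received all earlier assignments. In any 1:1 blocked scheme the arm that is behind is more likely to come next.

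What is at stake is whom the RC approaches next, and when. If those choices lean, even unconsciously, on the expected arm, the groups can differ in motivation or expected response. ANCOVA on the baseline score does not remove differences unrelated to that score. With 10 people per arm, participants who know their group and a self-rated primary outcome, the trial has little to absorb such a difference.

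**Working it through.** **Inputs from the article.** Ratio 1:1, blocked, size undisclosed (Study Design). Total N = 20 (Sample Size; it reproduces as 18 / 0.9 = 20). The RC consents everyone (Ethical Considerations) and obtains each assignment (Study Procedures). The article gives no figure for predictability, so there is none to reproduce.

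**Assumed.** Block sizes of 2 to 20, because the true size is withheld. A fixed size is used for the calculation only.

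**Step 1: guess rate under the present routing.** The rule is to guess the arm with fewer assignments so far and to toss a coin when the arms are level. Counts are level at the end of every balanced block, so the rule works without knowing the size. For a block of 4, the chance of a correct guess by position is:
- 1st: 1/2
- 2nd: 2/3
- 3rd: (2/3)(1/2) + (1/3)(1) = 2/3
- 4th: 1

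The sum is 2.833, and 2.833 / 4 = 70.8%, or 14.17 of 20.

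In general, a full block of 2h gives h + (4^h / C(2h,h) − 1)/2 correct guesses. For h = 1 this is 1.5 of 2 (75.0%). For h = 10 it is 10 + (5.676 − 1)/2 = 12.34 of 20 (61.7%). Sizes 6 and 8 do not divide 20, so the last, incomplete block is counted exactly.

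**Step 2: guess rate if the RC learns arms only at the post-training interview.** Study Procedures places the interview within 7 days of completing the intervention. Data collection runs about 12 months (Results). Subtracting about 4 months of follow-up per person (4 weeks plus 3 months) leaves about 8 months for accrual. With even accrual, 8 months is about 243 days, and 243 / 20 is about 12 days between participants. Five weekly sessions take about 35 days, and 35 / 12 = 2.9, so the latest 3 arms are unknown at each consent. The abstract's 4-week period gives 28 / 12 = 2.3, so a lag of 2 is shown as well.

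For a block of 4 with a lag of 3, only completed blocks or earlier, unrelated assignments are known at each position, so the rate is exactly 50%. With a lag of 2, only the 4th position gains: (3 × 1/2 + 2/3) / 4 = 54.2%.

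| Assumed block size | Correct of 20, now | Rate now | Rate, lag 2 | Rate, lag 3 |
|---|---|---|---|---|
| 2 | 15.00 | 75.0% | 50.0% | 50.0% |
| 4 | 14.17 | 70.8% | 54.2% | 50.0% |
| 6 | 13.40 | 67.0% | 56.0% | 53.0% |
| 8 | 12.93 | 64.6% | 56.5% | 54.0% |
| 10 | 13.06 | 65.3% | 58.1% | 55.9% |
| 20 | 12.34 | 61.7% | 58.0% | 56.8% |

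The first two result columns are exact. The lag columns come from 200,000 simulated sequences per size with the same guessing rule.

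**Step 3: would randomly varying block sizes solve it?** With sizes drawn at random from 2/4, 4/6 or 2/4/6, a guesser who knows the set is right 71.9%, 68.5% and 69.7% of the time. That is about the same as a fixed block of 4. The routing is what matters.

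**The case against.** **Safeguards are stated.** An uninvolved statistician, an undisclosed block size and release only after T1 are good practice. They protect the current assignment and the baseline score. This stands, but none of them prevents a forecast made from past assignments.

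**A reader might infer that one fixed block size is used and that late assignments in each block are known in advance.** The article does not support this. It says only that the size is undisclosed, and whether sizes vary is a detail a condensed article may leave to the full randomization document. If the size were 4 and known from the start, about 6.7 of 20 assignments would be certain. For an ideal observer who sees every past assignment but must infer the size, the simulated figure is about 0.14 of 20 if sizes 2, 4, 6, 8 and 10 are all thought possible, 0.9 for 2, 4, 6, 10 and 20, and 3.3 for 2, 4 and 6. What stands is a better-than-chance guess, not certainty.

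**Room and motive to steer are limited.** The physiatrist, not the RC, is to raise the study with everyone eligible on the caseload. The conditions are uncommon, the entry criteria are mostly objective, and controls are trained after T2. ANCOVA also covers differences that the baseline score captures. All this lowers the likely bias, and it is why no bias figure is given. If every guess were acted on, the arm difference would be (2p − 1) times the prognostic difference between people enrolled under each expectation. The multiplier runs from 0.23 (p = 0.617) to 0.50 (p = 0.75), but nothing in the article informs the second factor.

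**Re-routing only delays the RC's knowledge.** True, but Step 2 shows that the delay removes most of the advantage.

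**Conclusion.** The point holds as a modest, avoidable weakness in a stated procedure. As written, the person who consents each participant knows all earlier assignments and can guess the next arm correctly about 62% to 75% of the time, without knowing the block size. The conclusion rests on three readings: that one RC fills both tasks (the article mentions only one), that assignments usually reach the RC before the next consent (plausible at about 12 days between participants), and that the sequence is blocked 1:1 (stated). The guess rates depend on assumed block sizes; the size of any resulting bias is unknown. Nothing in the article suggests that steering has occurred.

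**What to change.** In Study Procedures, change who receives the assignment. Once consent and T1 are complete, the statistician sends it to the trainer, who already receives participants' contact details, and the trainer informs the participant. The RC confirms to the statistician that T1 is done but is not told the arm, and learns it only when the post-training interview is due.

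No extra staff are needed and the allocation list is unchanged, so this can be adopted for the remaining participants even though recruitment has begun. The cost is that the RC coordinates visits without knowing current assignments, and still learns each one after a delay of several weeks. If recruitment is already complete, the trial report should state who knew which past assignments at the time of each consent.

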### Ethical Considerations

The protocol for this study was approved by the Research Ethics Boards in rehabilitation and social integration of the Centre Intégré Universitaire de Santé et de Services Sociaux de la Capitale-Nationale (CIUSSS-CN; 2025-3100). The study protocol was registered on ClinicalTrials.gov (NCT06596850). Informed consent will be obtained from all participants by a research coordinator (RC). Participants will be made aware that they can withdraw from the study at any moment without facing any consequences. All collected information will remain strictly confidential within the limits established by law. To protect privacy and confidentiality, participants will be identified by a unique code, and their data will be anonymized and securely stored on a password-protected server. Participants will receive financial compensation for data collection activities to acknowledge their time and reduce attrition (CAD $50, equivalent to US $36, after each assessment session).

### Participants and Recruitment

Convenience sampling will be used to recruit 20 community-dwelling people with ARSACS or MD1 who use manual wheelchairs. Active recruitment strategies will include recruiting through outpatient services at the local rehabilitation center in Quebec City (CIUSSS-CN). The chief of physiatry (author XR) who has clinical expertise in ARSACS and MD1 will discuss the study with all individuals on his case load who have a diagnosis of ARSACS or MD1 and use manual wheelchairs. In addition, participants from a longitudinal study on ARSACS (completed in 2022) will be contacted and informed of the study. Passive recruitment strategies will include disseminating promotional videos on the social media and websites of Muscular Dystrophy Canada, other collaborators, and community organizations. Participants will be 18 years of age or older; have a diagnosis of ARSACS or MD1; use a manual wheelchair for mobility (≥ 3 times/week for ≥ 8 hours/week); and be able to propel their manual wheelchair at least 10 meters. Individuals will be excluded if they anticipate a health condition or procedure that contraindicates training (eg, surgery) or if they are concurrently receiving or planning to receive other manual wheelchair training during the study.

### Sample Size

The sample size was powered to detect a statistically significant difference of 20% between groups using mean change scores from baseline to postintervention in wheelchair skills [27]. A large effect size (Cohen *d* =1.2) for the wheelchair skills training and a correlation between measures (*R*^2^) of 0.6 was used. With a significance level of α=.05 and 90% power, a sample size of 18 was required for a repeated measures analysis of covariance (ANCOVA) (*F* tests) with between-group factors, controlling for baseline score (including function and wheelchair experience), as calculated using G*Power [28]. Adjusting for a 10% loss to attrition, a total sample of 20 is required (10 per group).

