### Data Analysis

Summary statistics (means, standard deviations, frequencies, and percentages) will be used to describe the sample. Details of adherence and intervention fidelity will be summarized. Assumptions for parametric testing of quantitative data will be verified, and the data will be screened for outliers [45]. An intention-to-treat analysis will be prioritized (with a per-protocol analysis reported depending on adherence and fidelity), and missing data will be addressed using multiple imputation methods for repeated measures of longitudinal data [46].

To address the primary objective, T2 WST performance scores will be compared between the experimental and control groups using ANCOVA or its nonparametric equivalent, with baseline scores used as the covariate. Variance (*R*^2^), statistical significance (95% CI), and effect sizes (partial η^2^) will be assessed using sums of squares methods. Secondary objectives will be evaluated using linear mixed-effect models, which are flexible to explore within-participant mixed/random effects [47].

Post-hoc exploratory analyses will investigate the influence of age, gender, diagnoses (ataxia or dystrophy), and manual wheelchair experience on effect size using linear mixed-effect models. Comparisons between WST-Q-M within-participant change scores for the experimental group (T1-T2) and WST-Q-M within-participant change scores after training in the control group (T2-T3) will be explored using *t* tests. Sensitivity analyses will be conducted on demographic variables (eg, age, sex, gender, and diagnoses) to generate hypotheses and inform future investigations.

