A multifaceted knowledge translation strategy will be used to increase awareness and knowledge to change practice for manual wheelchair skills training for people with ARSACS and DM1. Targeted materials for health care professionals will include infographics, podcasts, and video capsules that will be launched through the international PROSPAX (Progression Chart of Spastic Ataxias) initiative on recessive ataxias and neuromuscular disorders ([name]), including Rare Disease Day. Materials will be shared through clinical and community platforms including websites and social media of Muscular Dystrophy Canada, Groupe de Recherche Interdisciplinaire sur les Maladies Neuromusculaires, and the Wheelchair Skills Program. Lunchtime presentations and manual wheelchair training workshops will be planned with clinicians. Academic dissemination will include a minimum of 2 peer-reviewed articles and 2 national/international conferences. Led by the corresponding author ([name]), all study investigators will have access to the final data set and will be eligible for authorship.

This study has limitations that should be considered. Although the sample size is powered for the primary outcome, we do not have the power to detect changes in secondary outcomes or for subgroup analysis to explore the influence of potentially confounding factors. Considering the population under study, there may be an increased risk of attrition due to fatigue or difficulty in scheduling training/testing sessions within the desired time frame. We hope to mitigate these issues by offering validated questionnaire versions of tests and by providing training in the community to overcome transportation challenges associated with commuting to a research center. Given that wheelchair configuration and positioning are outside the scope of the WSTP, we will not consider wheelchair configuration or positioning in this study. However, these factors may have an impact on manual wheelchair skill performance and capacity, and ultimately on the efficacy of the intervention.

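### The sample size of 18 for 90% power does not follow from the repeated measures procedure named, and for the planned ANCOVA it holds only if 0.6 is R² and not a correlation

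*Protocol article*

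**What the plan says.** The Sample Size section sets the target as "a statistically significant difference of 20% between groups using mean change scores from baseline to postintervention". Its inputs are "A large effect size (Cohen *d* =1.2) for the wheelchair skills training", together with a value of 0.6 described in words as "for the wheelchair skills training and a correlation between measures" and followed at once by the symbol R². The result is "With a significance level of α=.05 and 90% power, a sample size of 18 was required for a repeated measures analysis of covariance (ANCOVA"), specified further as "F* tests) with between-group factors, controlling for baseline score", with function and wheelchair experience mentioned as part of the adjustment. The 18 is then raised to 20 for 10% attrition.

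The Data Analysis section plans a different primary test. T2 performance scores are compared between groups "using ANCOVA or its nonparametric equivalent, with baseline scores used as the covariate".

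The limitations paragraph of the Discussion relies on the calculation: "Although the sample size is powered for the primary outcome".

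**The concern.** There are two separate faults in the printed text.

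- **One number, two meanings.** A correlation of 0.6 gives R² = 0.6² = 0.36. An R² of 0.6 gives r = √0.6 = 0.775. The residual variance left after adjusting for baseline is 64% in the first case and 40% in the second, and required sample size depends directly on it.
- **One calculation, another analysis.** A repeated measures test of a between-group factor compares the groups on the average over the measurement occasions, baseline included. The planned ANCOVA compares T2 scores adjusted for baseline. The same 0.6 works in opposite directions: a higher correlation lowers power in the first test and raises it in the second.

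With about 20 people with rare disorders, a null result will be read against the claim that the trial had 90% power. For the planned test, the type II error risk at d = 1.2 is either about 16% or about 4%, and the text does not let a reader tell which.

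**Working it through.** **Inputs.** From Sample Size: α = .05, power 90%, d = 1.2, the value 0.6, F tests, 18 completers, 10% attrition. From Study Design: 1:1 allocation. From Data Analysis: T2 ANCOVA with baseline as covariate. For two equal groups f = d/2 = 0.6, so f² = 0.36. Sidedness is not stated, but an F test on two groups (1 numerator df) is two-sided, so α is taken as two-sided. Here d is taken as the between-group difference in units of the unadjusted SD. This is an assumption, since the article gives no SD. Power is from the noncentral F distribution with noncentrality λ.

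**Step 1. Attrition.** 18/(1 − 0.10) = 20. This reproduces.

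**Step 2. The procedure named in Sample Size** (repeated measures, between factors, m measurements, correlation ρ): λ = N f² m/[1 + (m − 1)ρ], df = 1 and N − 2.

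- m = 2, ρ = 0.6: λ = 18 × 0.36 × 2/1.6 = 8.1; power 0.762; N for 90% = 26.
- m = 3, ρ = 0.6: λ = 18 × 0.36 × 3/2.2 = 8.84; power 0.797; N for 90% = 24.
- With ρ = 0.775 it does worse: power 0.718 (m = 2) or 0.737 (m = 3), and 28 needed at 1:1.

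The named procedure therefore does not return 18 on either meaning of 0.6.

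**Step 3. The planned primary analysis** (T2 ANCOVA, one covariate): λ = N f²/(1 − R²), df = 1 and N − 3.

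- 0.6 is r, so R² = 0.36: λ = 18 × 0.36/0.64 = 10.1; power 0.844; N for 90% = 21, or 22 at 1:1.
- 0.6 is R²: λ = 18 × 0.36/0.40 = 16.2; power 0.964; N for 90% = 15, or 16 at 1:1.

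Allowing up to three covariates, because Sample Size mentions function and wheelchair experience, changes little: power at 18 is 0.836 to 0.844 for r = 0.6 and 0.960 to 0.964 for R² = 0.6.

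**Step 4. Unadjusted change scores**, because Sample Size mentions mean change: λ = N f²/[2(1 − r)], df = 1 and N − 2.

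- r = 0.6: λ = 18 × 0.36/0.8 = 8.1; power 0.762; N = 26.
- r = 0.775: λ = 18 × 0.36/(2 × 0.2254) = 14.4; power 0.945; N = 16.

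**Step 5. Summary (two-sided).**

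| Reading | Power at 18 | N for 90% |
|---|---|---|
| Named procedure, correlation 0.6, 2 measurements | 76% | 26 |
| Named procedure, correlation 0.6, 3 measurements | 80% | 24 |
| Planned T2 ANCOVA, r = 0.6 | 84% | 21 (22 at 1:1) |
| Planned T2 ANCOVA, R² = 0.6 | 96% | 15 (16 at 1:1) |
| Unadjusted change, r = 0.6 | 76% | 26 |
| Unadjusted change, r = 0.775 | 94% | 16 |

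None of these readings returns exactly 18.

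**The case against.** The strongest reply is that the symbol R² is printed. Read with the ANCOVA in Data Analysis, it makes 18 more than enough: 16 suffice at 1:1, and power at 18 is about 96%. This stands. A reader might infer from the mismatch that the 90% claim fails on every reading or has no support. The documents do not bear that out, because the R² reading meets it with margin. So does an unadjusted change-score comparison at r = 0.775.

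Second, the wording on mean change is not in itself a conflict. An ANCOVA of the T1 to T2 change adjusted for baseline gives the same group effect and the same test as an ANCOVA of T2 adjusted for baseline. This stands too. Only an unadjusted change-score test gives the lower 76%, and the primary analysis does not plan one.

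Third, a one-sided ANCOVA at r = 0.6 needs 18 at 1:1, with about 92% power, and the hypothesis in the Introduction is directional. But the section specifies F tests, which are two-sided for two groups, and nothing states a one-sided α. This may be how 18 arose, but the text does not say so.

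Fourth, with three covariates, 18 reaches 90% once total R² is about 0.48. That is correct, but it again presupposes that 0.6 is an R².

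Fifth, the shortfall is modest. On the r reading the planned ANCOVA has 84% at 18 and 88% (0.885) if all 20 complete. This limits the consequence, but the stated figure would still be wrong.

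A reader might also infer power as low as 66%, with 32 needed. That requires d = 1.2 to be already on the covariate-adjusted scale, which the article does not say. It is a reason to state the scale of d, not an estimate of the trial's power.

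**Conclusion.** The point holds as a fault in the stated basis for the sample size. The one value 0.6 is labelled as two different quantities, and the procedure named is not the planned primary analysis and does not give 18. For the analysis that will be run, power with 18 completers is about 84% if 0.6 is r and about 96% if it is R². The 90% claim therefore depends on which label is right. These figures assume two-sided α = .05, d on the unadjusted scale and equal arms. The attrition step is correct. The finding does not show that the trial is too small, and it does not call for more participants.

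**What to change.** In Sample Size, state whether 0.6 is r or R², and whether d = 1.2 is in units of the unadjusted or the baseline-adjusted SD. Replace the repeated measures between-factors procedure with the T2 ANCOVA from Data Analysis, and name the covariates it assumes. Restate the power for 18 completers, with d on the unadjusted scale: about 84% if r = 0.6, about 96% if R² = 0.6. The reference to mean change can stay if it is said to mean baseline-adjusted change. Align the limitations sentence in the Discussion with the restated figure. Keep N = 20.

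The cost is one reworded paragraph and one sentence, with no extra participants and no change in conduct. The downside is that the stated power may fall below 90%. If the sponsor confirms R² = 0.6 and d on the unadjusted scale, the 90% claim stands and only the description changes.
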